#### Consent

For the baseline survey, written informed consent was sought from the primary caregivers before the initiation of interview.

Informed consent will be sought from all the LHSs and LHWs when the intervention is rolled out.

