**Methods/Design:**

NIGRAAN is a cluster-randomised trial in District Badin, Pakistan. There are approximately 1100 LHWs supervised by 36 LHSs in Badin. For this study, each LHS serves as a cluster. All LHSs working permanently in Badin who regularly conduct and report field visits are eligible. Thirty-four LHSs have been allocated to either intervention or control arms in a ratio of 1:1 through computer-generated simple randomisation technique. Five LHWs from each LHSs are also randomly picked. All 34 LHSs and 170 LHWs will be actively monitored. The intervention consists of training to build LHS knowledge and skills, clinical mentorship and written feedback to LHWs. Pre- and post-intervention assessments of LHSs, LHWs and community caregivers will be conducted via focus group discussions, in-depth interviews, knowledge assessment questionnaires, skill assessment scorecards and household surveys.

Primary outcome is improvement in CCM practices of childhood diarrhoea and pneumonia and will be assessed at the cluster level.

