**Overview of NIGRAAN sampling strategy for baseline survey.**

#### Allocation to intervention

LHSs were allocated to clusters based on a parallel design with 1:1 ratio. The allocation of 34 LHSs to intervention/control arm clusters was blinded at the cluster level and carried out through computer-generated randomised tables in computer software MS Excel. The process was carried out by a person not otherwise involved in the study.

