#### Blinding

After assignment to intervention and control clusters, all participants, field staff, independent evaluators (IEs), and data entry personnel will be blinded. For this purpose, control and intervention cluster LHSs and LHWs will be assigned study IDs with the key available only to the core Aga Khan University research team.

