#### A. Training

In a 4-day training workshop, a training consultant would facilitate the 17 LHSs in the intervention arm to improve their theoretical and practical understanding of management of childhood diarrhoea and pneumonia and clinical mentoring and supervision skills. Special focus would be to improve LHS skills in providing verbal and written feedback to their assigned LHWs. The face-to-face learning would be complemented by hands-on training in the hospital setting along with practical exercises in a simulated environment. The instructional methodologies used during the training would include interactive lectures complemented with audio-visual aids/videos (to be sourced through WHO) and role plays, etc. Prior to the NIGRAAN specific training (described above), a 2-day refresher training based on all aspects of existing LHW curriculum would be offered by master trainers (trained through the project) for all the 34 LHS in both arms.

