#### B. Supervisory tools

To complement the existing LHW Management Information System, NIGRAAN intervention will also introduce the following tools:The ‘Modified Supervisory Checklist’ has been adapted from the existing LHW-P Management Information System kit for LHSs. It augments certain components to strengthen the monitoring of community case management of LHWs by LHSs and adds the feature of direct observation.The ‘Supervisor’s Tally Sheet for Compilation of Quality of Case (QoC) Management’ is the consolidated version of the modified supervisory checklist providing at a glance view of the progress and quality of case management as well as picks up the gaps in case management practices of LHWs working under a given LHS.The ‘LHS Feedback Card’ for individual LHWs is the most important tool in the intervention package. It aims to introduce the practice of written feedback to be provided to LHWs through LHSs.

Various components of NIGRAAN intervention package are shown in Figure 4.

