## Trial status

Pre-intervention phase has concluded. Preparation for installing surveillance is on-going so that cases can be identified for starting the intervention. Recruitment in control and intervention arm of the study will start at the end of November 2014 and continue for the next 9–12 months.

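### Consent of supervisors and workers is placed at roll-out, after allocation, where study-ID blinding cannot hide the arm, so refusal may depend on arm and bias the LHS and LHW outcomes.

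*Protocol article*

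**What the plan says.** Allocation is reported as complete. The abstract (Methods/Design) says "Thirty-four LHSs have been allocated to either intervention or control arms in a ratio of 1:1", and the section Allocation to intervention, also in the past tense, says "The allocation of 34 LHSs to intervention/control arm clusters was blinded at the cluster level".

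Consent of the health workers is still to come. The Consent section says "Informed consent will be sought from all the LHSs and LHWs when the intervention is rolled out". Caregivers are treated separately: they gave their own written consent before the baseline interview.

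The Blinding section says "After assignment to intervention and control clusters, all participants, field staff, independent evaluators (IEs), and data entry personnel will be blinded", by means of study IDs whose key stays with the core research team.

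The intervention sections describe activity in one arm only. Under A. Training: "In a 4-day training workshop, a training consultant would facilitate the 17 LHSs in the intervention arm". Under B. Supervisory tools, of the feedback card: "It aims to introduce the practice of written feedback to be provided to LHWs through LHSs". A 2-day refresher for all 34 LHSs in both arms comes before the workshop.

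Under Study participants, a caregiver qualifies by living in the coverage area of an LHW who has been enrolled in the study. Table 2 measures the primary outcome by baseline and end-line household surveys, and the two secondary outcomes by knowledge questionnaires and skills scorecards completed on LHSs and LHWs, alongside qualitative tools.

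**The concern.** When people are asked to take part after their cluster has been allocated, and can tell which arm they are in, participation becomes a post-randomisation choice. Randomisation balances the 34 LHSs as allocated. It does not balance the subset who agree after learning what their arm involves.

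The arms differ in what they ask of staff. Intervention LHSs take on a workshop, a modified checklist, a tally sheet and written feedback, and their LHWs are observed and given feedback more closely. Under Potential harms and mitigation the authors themselves allow, as a remote possibility, that this could raise work stress. If the more burdened or less confident staff decline in one arm and their counterparts stay in the other, scores can differ between arms without any effect of the intervention.

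This falls directly on the knowledge and skill outcomes, because a worker who declines cannot be assessed. It could extend to the household survey through the eligibility wording.

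**Working it through.** **Order of events**

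| Step | Where stated | Timing |
|---|---|---|
| 34 LHSs allocated 1:1 | Abstract; Allocation to intervention | done |
| Baseline household survey, caregiver consent | Consent; Trial status | done |
| LHS and LHW consent | Consent | future, at roll-out |
| Refresher, all 34 LHSs | A. Training | future, both arms |
| 4-day workshop, tools, feedback cards | A. Training; B. Supervisory tools | future, intervention arm only |

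Consent therefore follows allocation. The article does not say whether it falls before or after the first arm-specific step. Having an uninvolved person generate the allocation protects the sequence, but it does not prevent refusal afterwards. Study IDs can mask evaluators and data entry staff. They cannot mask an LHS who is, or is not, called to the workshop.

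**The plan's own figures** (Sample estimates)

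- LHWs: 17 × 5 = 85 per arm, and 2 × 85 = 170.
- Households: 85 × 100 = 8,500 per arm; 8,500 / 4 = 2,125; 2,125 / 17 = 125 per cluster.
- The 17 clusters per arm cannot be reproduced, because no effect size is given with the intra-cluster correlation (ICC) of 0.122 and 80% power. The power figures below therefore take 17 v 17 as giving exactly 80%.

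**Power if clusters are lost from one arm only** (two-sided 5% assumed, normal approximation)

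With k clusters in one arm and 17 in the other, the ratio of effect to standard error is (1.960 + 0.842) × √[2k / (k + 17)]. The design effect cancels, so the result does not depend on cluster size. Power is Φ(ratio − 1.960).

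| Clusters | 2k/(k+17) | Power |
|---|---|---|
| 16 v 17 | 32/33 = 0.970 | 78.8% |
| 15 v 17 | 30/32 = 0.938 | 77.4% |
| 14 v 17 | 28/31 = 0.903 | 75.9% |
| 13 v 17 | 26/30 = 0.867 | 74.2% |

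**Shift in an arm's mean from selective refusal**

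If a fraction f declines and those who stay score g higher than those who decline, the mean of those who stay exceeds the full arm's mean by f × g. The article gives neither f nor g. Assume 1 to 3 of 17 LHSs decline and g is 10 to 30 percentage points:

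- smallest: 1/17 × 10 = 0.6 points
- middle: 2/17 × 20 = 2.4 points
- largest: 3/17 × 30 = 5.3 points

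The same fractions apply to LHWs (5 of 85 is 1/17). The shift favours the intervention if weaker intervention staff decline, and works against it if stronger ones do.

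**Household survey, only if refusers' households are dropped**

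The design effect is 1 + 124 × 0.122 = 16.128, so the effective size is 2,125 / 16.128 = 131.8 per arm. From an assumed control rate of 38% or 41% (the national treatment coverages in the Background), the difference detectable with 80% power is about 17 points. A shift of 0.6 to 5.3 points is to be read against that. If the households are kept, the shift from this source is zero.

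**The case against.** Four points weigh against the concern.

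1. **Knowledge of arm at consent is not stated.** A reader might infer that staff consent knowing their arm. The documents do not say so. The Consent section describes one step for all LHSs and LHWs, the Blinding section says participants are blinded, and the common refresher precedes the workshop. If roll-out means the start of phase II, consent could come before any arm-specific activity. This stands as far as it goes. But the text also permits consent at or after the point where the arms diverge, and from then on the stated blinding cannot hold for LHSs, or for LHWs once feedback cards appear.

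2. **Refusal may be rare.** LHSs are permanent employees, LHWs are salaried, the provincial health department agreed to implement the project, and the work is described as within existing duties. The added stress is called only remotely possible. This stands: nothing in the article points to substantial refusal.

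3. **The primary outcome has its own consent.** Caregivers consent for themselves, and the pre-intervention phase ended before any worker consent at roll-out. A reader might infer that the primary comparison is biased. The only textual route is the eligibility phrase about an enrolled LHW, which may simply mean the 170 selected LHWs. This also stands, and limits the direct risk to the LHS and LHW outcomes.

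4. **The Trial status section is weak support.** It says "Recruitment in control and intervention arm of the study will start at the end of November 2014" and gives 9–12 months for it. That may describe recruitment of illness cases through surveillance, so the point does not rest on it.

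The absence of a rule for handling refusals in the analysis is not raised, since a condensed article may leave that to the full protocol or analysis plan.

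**Conclusion.** The point holds in limited form. The stated timing puts LHS and LHW consent after allocation and at the stage where the arms become visibly different, and the stated blinding cannot prevent arm-dependent refusal there. The direct exposure is selection bias in the two secondary outcomes measured on LHSs and LHWs. The primary outcome is exposed only under one reading of the caregiver eligibility wording.

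The loss of power is modest: 78.8% or 77.4% if one or two clusters leave one arm, taking 17 v 17 as 80%. A reader might compute a larger drop by removing clusters from both arms, but that describes equal loss, not the unequal loss at issue here. The possible shift in an arm's mean, 0.6 to 5.3 points, rests wholly on assumed refusal of 1 to 3 of 17 and an assumed gap of 10 to 30 points. It shows scale and predicts nothing. The change is still worth making, because roll-out was still ahead when the article was written and the remedy costs little.

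**What to change.** Three changes to the text:

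- **Consent.** State that consent is obtained from all 34 LHSs and 170 LHWs on one common form, before any of them is told the arm and before any arm-specific activity, at the latest at the common refresher.
- **Community caregivers.** Define eligibility by the catchments of the 170 selected LHWs. End-line households in all 34 allocated clusters are then surveyed with the caregiver's own consent, whether or not the LHS or LHW agrees to be assessed.
- **Reporting.** Give the number of LHSs and LHWs who decline, by arm.

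Allocation itself need not be repeated. The cost is a slightly earlier consent visit, a single form for both arms and a few sentences of text.

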#### Blinding

After assignment to intervention and control clusters, all participants, field staff, independent evaluators (IEs), and data entry personnel will be blinded. For this purpose, control and intervention cluster LHSs and LHWs will be assigned study IDs with the key available only to the core Aga Khan University research team.

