## Methods

### Study design

This is a cluster randomised intervention trial consisting of three sequential phases:Pre-intervention: phase IFocus group discussions (FGDs) and in-depth interviews (IDIs) explore stakeholders’ (LHS/LHWs/policymaker) perspectives about the structural gaps in the LHW-P and health workers’ basic knowledge and skills related to CCM of childhood diarrhoea and pneumonia, etc. The findings would help to build an optimised intervention addressing deficient areas of knowledge and skills in the next phase. The baseline household survey (administered through a structured questionnaire) has been simultaneously administered to identify community caregivers’ practices related to childhood diarrhoea and pneumonia.An active case surveillance with a Global Positioning System (GPS) will also be initiated to identify, track and follow up all reported cases of childhood pneumonia and diarrhoea from the catchment households of randomly selected five LHWs/LHSs in both arms of the study (total 170 LHWs/34 LHS). Upon case identification, this surveillance will help to sample LHS and LHWs for assessment of their knowledge and skills related to CCM of diarrhoea and pneumonia. Knowledge assessment questionnaires (KAQs) and scorecards will be used for this purpose.Data obtained through baseline survey, scorecards, KAQs, FGDs and IDIs will be analysed to get consolidated results for the pre-intervention phase.Intervention: phase IIPhase II incorporates the refresher training of all LHS and execution of NIGRAAN specific intervention package (described below) for 9–12 months. The active case detection continues during this phase for periodic skill assessment of health workers through scorecards and KAQs and to distribute written feedback cards to LHWs as part of the NIGRAAN intervention package.Sample FGDs and IDIs will track the uptake of intervention by all stakeholders.Post-intervention: phase IIIPhase III includes an end-line household survey and qualitative data collection through FGDs and IDIs to identify barriers and enablers for NIGRAAN implementation and scale up.All the data obtained through the surveys, scorecards, KAQs, FGDs and IDIs during intervention and post-intervention phases will be analysed and results synthesised through method triangulation. Figure 2 provides an overview of NIGRAAN study phases.

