#### Quantitative instruments

Skills assessment scorecard A: lists the variables for assessing clinical case management skills of LHWs and LHSs. Each item on the scorecard is linked with the essential tasks related to CCM of pneumonia and diarrhoea in children under 5.Skills assessment scorecard B: will be used for assessing supervisory and clinical mentorship skills of an LHS. This will incorporate elements of clinical mentoring and supportive feedback.‘Independent evaluators’ with relevant background and training in community health and clinical care will be recruited to accompany the health workers during her home visits and fill the scorecards.Household survey questionnaire: will be used for baseline and end-line household survey to collect data on caregiver knowledge and practices.Knowledge assessment questionnaire: will be used to assess LHS and LHW knowledge regarding CCM of pneumonia and diarrhoea in children under five. This instrument, in addition to being deployed pre intervention, will also be used periodically to assess change in LHS and LHW knowledge and skills.Table 1 provides an overview of the various quantitative tools.

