**Table 1 Tab1:** **Overview of NIGRAAN quantitative tools**

**Tools/instruments**	**Purpose**	**User(s) in the field**
*Household survey questionnaire*	To record the socio-demographic information and caregiver practices regarding diarrhoea and pneumonia of the population under study as well as to document the morbidity due to diarrhoea and pneumonia	*The data collection team*
*Knowledge assessment questionnaire*	To assess the theoretical understanding and knowledge of LHSs and LHWs regarding community case management of diarrhoea and pneumonia	*The research team*
*Skills assessment scorecard ‘A’*	To assess the practical/clinical skills of LHSs and LHWs regarding community case management of diarrhoea and pneumonia	*Independent evaluator(s)*
*Skills assessment scorecard ‘B’*	To assess the supervisory and clinical mentoring skills of LHSs in terms of providing feedback and supportive supervision to LHWs	*Independent evaluator(s)*

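### The blinding claim cannot hold for the supervisors and health workers and is not credible for the independent evaluators, which leaves the secondary outcomes open to detection bias

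*Protocol article*

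**What the plan says.** The Blinding section says that once clusters are assigned, "all participants, field staff, independent evaluators (IEs), and data entry personnel will be blinded". The means is that LHSs and LHWs are "assigned study IDs with the key available only to the core Aga Khan University research team". No other masking device is described.

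The intervention has two parts. Under A. Training, in a 4-day workshop "a training consultant would facilitate the 17 LHSs in the intervention arm". A separate 2-day refresher on the existing curriculum is given first "for all the 34 LHS in both arms". Under B. Supervisory tools, the package adds a modified checklist, a tally sheet and a feedback card. Of the card, the article says: "It aims to introduce the practice of written feedback to be provided to LHWs through LHSs".

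For measurement, Quantitative instruments says that independent evaluators will "accompany the health workers during her home visits and fill the scorecards". Scorecard A covers clinical case management and scorecard B covers supervision, mentoring and feedback. Table 1 gives the purpose of the knowledge assessment questionnaire (KAQ) as "To assess the theoretical understanding and knowledge of LHSs and LHWs regarding community case management of diarrhoea and pneumonia" and names the research team as its user. Table 1 assigns the household survey to the data collection team, and Table 2 makes that survey the measure of the primary outcome.

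**The concern.** A coded ID can mask a data file, or a person who meets a participant only through that file. It cannot hide an intervention from those who deliver it, those who receive it, or someone standing beside them while it happens. If the raters of skills and mentoring can tell the arms apart, their scores may lean towards the intervention. A reader who trusts the blinding statement would then wrongly rule that bias out.

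The scorecards and the KAQ are the only quantitative measures that Table 2 lists for the two secondary outcomes. The Primary outcome section also presents LHS and LHW knowledge and skills as the route by which case management is meant to improve. Biased scores would therefore distort the trial's account of how the intervention works, even if the primary comparison were sound.

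**Working it through.** No arithmetic applies, because the question is whether the blinding statement agrees with the rest of the article. Each group is taken in turn.

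- **LHSs (17 per arm, 34 in all).** The 17 in the intervention arm attend a 4-day workshop and then use new tools. The refresher is common to both arms, but it covers the existing curriculum and is not a sham for the workshop or the tools. An intervention LHS knows what she attended and what she hands out. Blinding is untenable.
- **LHWs (5 per LHS, 85 per arm, 170 in all).** Those in intervention clusters receive a written card, a practice the article says it is introducing. Potential harms and mitigation expects workers to notice the move from verbal to written feedback. Qualitative instruments plans to ask about the usefulness of the intervention. Both assume awareness. Blinding is untenable.
- **Independent evaluators, scorecard B.** They observe in person and score mentoring and feedback, which is the behaviour the intervention is meant to change. Under Study design, case detection in phase II supports periodic skill assessment and also serves "to distribute written feedback cards to LHWs as part of the NIGRAAN intervention package". An evaluator who sees a card has a strong cue to the arm. That she will see one is an inference, but a strong one.
- **Independent evaluators, scorecard A.** The same people rate on home visits, but the items are tied to essential case management tasks and not to feedback. The exposure is real but smaller.
- **KAQ.** Table 1 names the research team as user; the Blinding section gives the key to the core research team. The article neither says that these are the same people nor separates them. The exposure is conditional on overlap.
- **Household survey interviewers and data entry staff.** They have no stated part in delivering the intervention, and coded IDs can mask them. The claim can hold for these groups.

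The Plan of data analysis compares pre-to-post changes between arms. Phase I assessments come before the workshop and cards, so no such cue exists then. A rating bias that enters only in phase II is not removed by subtracting a baseline.

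The Discussion names one measurement limitation, the effect of being observed on LHW performance. It does not mention raters' awareness of arm.

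**The case against.** The strongest reply is that the primary outcome is not touched in the same way. It rests on a household survey done by a team that Table 1 lists separately from the evaluators, and that team can be masked. This stands, and it limits the point to the secondary outcomes.

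A second reply is that seeing supervision does not by itself reveal the arm. Routine care already includes it: the Background reports that 40% of LHWs receive the required feedback, and the modified checklist is adapted from an existing one. This stands in part. It is why evaluator blinding is called not credible rather than impossible. It does not cover the written card, which is new.

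A third reply is that scorecard A and the KAQ are not described as subjectively scored. That is fair, and they should not be treated as equal to scorecard B.

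Two stronger readings are tempting. A reader might infer that nobody in the trial can be blinded; the documents do not support this for survey interviewers or data entry staff. A reader might also infer that key holders give the KAQ; the article says research team in one place and core research team in another, which leaves overlap possible but does not establish it.

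**Conclusion.** The blinding statement is wrong for LHSs and LHWs and not credible for independent evaluators. This rests on the plain reading that the supervisory tools, listed as components of the intervention, are used only in intervention clusters, and on the absence of any sham workshop or sham tools in the article.

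In scope, the quantitative measures of both secondary outcomes are affected, in the order scorecard B, then scorecard A, with the KAQ depending on who gives it. The size of any bias cannot be stated. The article gives no figure for rater drift, and its intra-cluster correlation of 0.122 is not tied to the scorecards, so a standardised effect built on it would be false precision.

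A reader might infer that the primary result is compromised. The documents do not support that, provided the survey team is in fact kept masked. The statement should be corrected, but this is not a flaw that undermines the primary comparison.

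**What to change.** Replace the blinding statement with one that goes group by group:

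- LHSs and LHWs are not blinded.
- Independent evaluators cannot be assumed to be blinded.
- Household survey interviewers and data entry staff are masked by coded IDs, and are kept separate from the evaluators and from the allocation key.
- The KAQ is given and marked by existing staff who do not hold the key.
- Scorecard results, scorecard B in particular, are not presented as blinded evidence of effect, and raters' possible awareness of arm is added to the limitations.

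The cost is a change of wording and the re-tasking of some existing staff; the sample size and the intervention are unchanged. The trial gives up its claim of full blinding. The Trial status section places the start of recruitment in both arms at the end of November 2014, with 9–12 months to follow, so on the article's own timetable most phase II assessment was still ahead when it was published in December 2014.
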